### Implementation {16c}

An independent researcher will generate the allocation and directly informs the treatment team by e-mail about the treatment arm that families receive according to the randomization list. The therapist informs the families.

## Assignment of interventions: blinding

### Who will be blinded {17a}

Until randomization, both families and therapists are blind to the treatment allocation to mitigate bias due to expectation or disappointment. Nobody will be blinded during the intervention.

### Procedure for unblinding if needed {17b}

The design is open-label, and only data analysts will be blinded. Unblinding will therefore not occur.

### Data collection and management

#### Plans for assessment and collection of outcomes {18a}

The instruments with the best psychometric qualities and sensitivity to change in a short time period are selected for this study. For the primary outcomes different types of measurements are included: questionnaires for multiple informants, an interview and an observation task. A description of the study instruments can be found in the “Outcomes {12}” section. For this study, researchers will be trained and certified in the CAPS-CA interview and scoring protocol. The researchers will write a report based on the interview part of the CAPS-CA, and other answers are entered in a SPSS file. All data collected by questionnaires will be collected through an online survey system, Survalyzer, minimizing entry errors. Data will be stored and coded in a SPSS file. The FIT observation tasks will be administered according to a protocol and the recoded tasks will be coded by trained researchers with the use of a standard scoring form. For both the CAPS-CA and the FIT observation task, inter-rater reliability will be calculated for 20 participants. All data will be cleaned before analyses (e.g. checking on double entries, ranges, checking dates of data collections with treatment dates, coding missing data) in IBM SPSS.

#### Plans to promote participant retention and complete follow-up {18b}

It is common in trauma treatment that clients show avoidance behaviour because of the confrontation with anxiety-provoking details of the trauma. To prevent drop out psycho-education about avoidance behaviour and the disadvantages of avoiding is offered during treatment. To detect drop out of selective groups, participants who discontinue the treatment program will be asked to continue measurements.

#### Data management {19}

All research data will be handled confidentially and will be stored in closed facilities, which can only be assessed by researchers. The research data is confidential and will not be provided to third parties. Privacy of the participants will be protected by allocating key codes to the personalia, which will only be traceable with a separate list. The key codes are 3-digit numbers ranging from 000 to 150 and will be given in consecutive order. This list with personalia (names, addresses, phone numbers) that connects the participants with the research data is exclusively accessible by two of the researchers via an encrypted file and will eventually be destroyed. DarkStor from DANS (Dutch research data repository) will be used to store sensitive data and ArchStor (local data archive of Vrije Universiteit Amsterdam) for datasets that can be used for possible future research projects.

During data collection records of all specifics about the collections (e.g. measurements, dates, details about participants) will be kept in a logbook.

#### Confidentiality {27}

The research data will be stored and managed by the research team. All employees who work with confidential data will sign a confidentiality agreement, on which they state not to share the information with third parties. The digitalized research materials and confidentiality agreements will be stored in a secured folder on the network of VU Amsterdam. Data will be stored for 15 years, according to Medical Ethical Committee guidelines or for 5 years after the last publication based on this data.

#### Plans for collection, laboratory evaluation, and storage of biological specimens for genetic or molecular analysis in this trial/future use {33}

No biological specimens will be collected or stored (see the “Additional consent provisions for collection and use of participant data and biological specimens {26b}” section).

## Statistical methods

### Statistical methods for primary and secondary outcomes {20a}

The measurement level of each variable is at least ordinal. We control for the duration and severity of family violence [96], child functioning, parental psychopathology [97], and new incidents of family violence as a priori potential confounders. Analyses will be performed using the latest version of the software package Statistical Package for the Social Sciences (SPSS). First, to determine whether changes on continuous measures are different per treatment, we use linear mixed models. Continuous measures with only one time point will be analysed with independent samples *T*-test. Changes in categorical outcomes over the course of treatment across the conditions are tested with generalized estimating equations (GEE). To handle missing data, we will use maximum likelihood estimation within the linear mixed model analyses. For the planned GEE, we will explore the possibilities to deal with missing data, depending on the amount, randomness, and type of data missing. Analyses will primarily be performed according to the principles of intention-to-treat; however, they will be repeated as per-protocol analyses (see Table 4).

**Table 4 Tab4:** Statistical analyses

*Statistical analyses*					
	Measure	Type of data	Timepoints	Statistical analysis	Subjects
Child PTSD	CAPS-CA	Categorical	3	GEE	ITT/PP
	CRIES	Continuous	4	Mixed models	ITT/PP
	TSCC	Continuous	3	Mixed models	ITT/PP
Child functioning	SDQ	Continuous	3	Mixed models	ITT/PP
	CDI	Continuous	3	Mixed models	ITT/PP
	CDC	Continuous	3	Mixed models	ITT/PP
Parent functioning	NOSI-K	Continuous	4	Mixed models	ITT/PP
	Trauma-informed	Continuous	3	Mixed models	ITT/PP
	TSI	Continuous	3	Mixed models	ITT/PP
	YAS-R	Continuous	3	Mixed models	ITT/PP
	DPAS	Continuous	3	Mixed models	ITT/PP
Structural emotional and physical safety	CTS	Continuous	3	Mixed models	ITT/PP
	CTS-pc	Continuous	3	Mixed models	ITT/PP
	PRTI	Continuous	3	Mixed models	ITT/PP
	ACE-Q	Continuous	3	Mixed models	ITT/PP
	New IPV incidents	Continuous	4	Mixed models	ITT/PP
	SIS	Continuous	3	Mixed models	ITT/PP
	SIFS	Continuous	3	Mixed models	ITT/PP
	SIM-PR	Continuous	3	Mixed models	ITT/PP
	Security scales	Continuous	3	Mixed models	ITT/PP
	FIT	Categorical	1	Independent samples T-test	ITT/PP

Descriptive and exploratory analyses will be carried out by standard methods. All continuous scores will be examined for normality. If variable distributions deviate too much from normality, corrective steps will be taken either by transforming variables or by using non-parametric tests. We will control for child functioning, parental psychopathology, duration, severity, and intensity of interparental violence, and new IPV incidents. The variables are treated as covariables in the analyses mentioned below.

To examine our primary hypothesis, linear mixed models will be used in case of continuous data. GEE will be used for the categorical data. We will use the end of treatment (T12/T14) and intermediate/follow-up time-point (T13) to compare FITT with ITT (objective 1).

To examine our secondary hypotheses, linear mixed models will be used. We will use the end of treatment time-point (T12/T14) to compare FITT with TAU. Control measures are child functioning; parental psychopathology; duration, severity, and intensity of interparental violence; and new IPV incidents. The variables are treated as covariables in the up-mentioned analyses. We will use the Benjamini-Hochberg method to correct for multiple comparisons.

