##### Emotional security and physical safety

To assess the severity and intensity of the violence that children have been exposed to, a combined measure will be used including items from the Conflict Tactics Scale (78 items, 8-point rating scale) [64], the Conflict Tactics Scale parent child (27 and 39 items, 8-point rating scale) [64], the Parents Report of Traumatic Impact (21 items ) [65], and the Adverse Childhood Experience Questionnaire (10 items, 5-point rating scale) [66]. An example item is *I punched or hit my partner with something that could hurt*. This combined questionnaire has been used in a previous study on the effectiveness of a psycho-educational prevention program for children exposed to IPV [67]. The questionnaire covers the topics and duration of the violence and the nature of the arguments in the relationship with the (ex-partner), followed by items from the Conflict Tactics Scale parent child and Parents Report of Traumatic Impact about problems between parent and child, and traumatic events the child has experienced. The questionnaire also includes items about traumatic experiences in parents’ own childhood. A short questionnaire of 8 items for parent and child is added to assess if any new IPV incidents or other stressful events occurred.

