## Assignment of interventions: allocation

### Sequence generation {16a}

Random allocation to either condition is needed, in order to reduce selection bias and to be able to attribute effects to parenting training and family sessions added upon an intensive trauma therapy. After informed consent is provided, families will be randomly assigned within each site to one of the treatment conditions. Within the multicentre trial, families are randomized by an independent researcher, following a computer-generated list with each participant having a 33.3% chance of being assigned to FITT, ITT, or TAU. The results of the randomization are communicated to the site per participating family.

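### The primary and secondary models adjust for new violence incidents, a post-randomisation outcome that FITT aims to reduce, so they may not estimate the total treatment effect

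*Protocol article*

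**What the plan says.** The statistical methods section {20a} of the protocol article opens by naming its control variables, "and new incidents of family violence as a priori potential confounders" among them. It repeats the list further down: "We will control for child functioning, parental psychopathology, duration, severity, and intensity of interparental violence, and new IPV incidents". Two sentences set the scope. Before the primary hypothesis (FITT versus ITT; linear mixed models, with GEE for categorical outcomes) it says "The variables are treated as covariables in the analyses mentioned below". After the secondary hypotheses (FITT versus TAU; linear mixed models) it says "The variables are treated as covariables in the up-mentioned analyses". No analysis without these covariates is described for the models.

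The same variable is an outcome elsewhere. The outcomes section describes it under the primary outcomes, in the part on emotional security and physical safety: "A short questionnaire of 8 items for parent and child is added to assess if any new IPV incidents or other stressful events occurred". Table 3 schedules it at T0, T1–11, T12/14 and T13. Table 4 has a row "New IPV incidents" with four timepoints and its own mixed model.

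The description of FITT's family therapy, which ITT does not include, names better skills for avoiding escalation among its goals.

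**The concern.** A confounder of a treatment comparison must influence, or share a cause with, treatment assignment. Assignment here is random, so an incident that happens after allocation cannot play that role. It can be a consequence of treatment, and the protocol intends it to be one.

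Conditioning on a consequence of treatment has two effects. It blocks whatever part of the benefit runs through fewer incidents, so the treatment coefficient moves towards a direct effect. If an unmeasured factor drives both incidents and symptoms, conditioning also opens a non-causal path between treatment and outcome (collider bias), whose direction depends on that factor.

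The primary objective asks whether adding the family component yields a stronger reduction in symptoms and a stronger increase in safety, and the analysis is declared intention-to-treat. Both call for the total effect. The adjusted model could understate the family component for the very reason that it works as designed.

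**Working it through.** **1. The plan's own sample size.** Inputs from the sample size section {14}: f = 0.18, two groups, two measurements, correlation 0.5, ε = 1, two-sided 5%, power 80%.

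- Noncentrality: λ = f² × N × m / (1 − ρ) = 0.0324 × 64 × 2 / 0.5 = 8.29, with 1 and 62 degrees of freedom.
- Power is 0.809 at N = 64 and 0.797 at N = 62, so the stated 64 reproduces.
- Three arms of 32 make 96, and 96 / 0.8 = 120, the stated target.

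**2. What f = 0.18 means as a difference.** In a two-by-two group-by-time interaction the cell effects are ± one quarter of the between-group difference in change. So f = (difference / 4) / SD, and the difference is 4 × 0.18 = 0.72 SD. At ρ = 0.5 the SD of change, SD × √(2 × 0.5), equals the single-occasion SD, so 0.72 holds on either scale.

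**3. Loss through adjustment.** Let *a* be the reduction in incidents due to FITT (in SD) and *b* the slope of symptoms on incidents. In a linear model without an unmeasured common cause, the adjusted effect is the total minus *a* × *b*. The documents give neither path, so both are assumed.

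| *a* | *b* | Loss (SD) | Share of 0.72 |
|---|---|---|---|
| 0 | any | 0 | 0% |
| 0.36 | 0.3 | 0.108 | 15% |
| 0.36 | 0.5 | 0.180 | 25% |
| 0.3 | 0.2 | 0.060 | 8% |
| 0.5 | 0.4 | 0.200 | 28% |

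A simulation with a 0.72 SD total effect, *a* from 0.3 to 0.5 and *b* from 0.2 to 0.4 gave losses of about 9 to 28%, matching the last two rows within simulation error.

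**4. Adding an unmeasured common cause.** If such a factor loads *u* on both incidents and symptoms, the loss becomes *a* × (*b* + *u*²). With *u* = 0.4 (assumed):

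- 0.3 × (0.2 + 0.16) = 0.108, or 15%.
- 0.5 × (0.4 + 0.16) = 0.280, or 39%.

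The simulation gave 15 to 39%. Loadings of opposite sign would reduce the loss instead.

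**5. Effect on power at N = 64**, with residual variance held as planned:

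| Share removed | f | Power | N for 80% |
|---|---|---|---|
| 0% | 0.180 | 0.81 | 64 |
| 10% | 0.162 | 0.72 | 78 |
| 20% | 0.144 | 0.62 | 98 |
| 30% | 0.126 | 0.51 | 126 |

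Incidents that predict symptoms would also lower the residual variance and offset some of this. That would be a gain in precision for a different quantity.

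**The case against.** The best defence has four parts, and some of it stands.

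**The T0 value may be meant.** Table 3 does include T0. But the text does not restrict the covariate, past violence is already listed separately by duration and severity, and "new" reads naturally as arising during the study. If T0 was intended, the plan should say so.

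**The mediated path is limited.** This partly stands. Family therapy comes in week 4, so earlier incidents cannot reflect it, although parent therapy in weeks 2 and 3 might. TAU contains parenting work and, where indicated, family work with a similar aim, so the problem is more plausible for FITT versus ITT, the primary comparison.

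**The size is unknown.** This stands. A reader who takes the total effect as 2 × 0.18 = 0.36 SD would get a loss of 0.108 / 0.36 = 30% to 0.180 / 0.36 = 50%. The planned model is a group-by-time interaction, for which f = 0.18 means 0.72 SD, so those percentages are not supported. Collider bias likewise needs a common cause that the documents do not establish.

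**Wider readings go too far.** A reader might infer the following, and the documents do not support it:

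- *Every analysis is affected.* The FIT observation is compared by an independent-samples t-test, which carries no covariates.
- *Outcomes are adjusted for themselves.* Taken literally, new incidents, child functioning and parental psychopathology are both outcome and covariate. No analyst would fit a score on its own concurrent value, and the instrument and timepoint are details that an article may leave to the full plan.
- *Leaving out site costs precision.* Families are allocated by site ("families will be randomly assigned within each site to one of the treatment conditions"), but the structure of the mixed models is not given, and a constant site difference largely cancels in a group-by-time contrast.
- *The ACE-Q is an outcome that cannot change.* The article says "The questionnaire also includes items about traumatic experiences in parents’ own childhood" without identifying these as the ACE-Q items, so the link is inferred.

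**Conclusion.** The point holds for the mixed models and GEE behind the FITT versus ITT comparison and for the mixed models behind FITT versus TAU. The plan labels as a confounder a variable that mostly arises after randomisation, is a treatment target and is itself an outcome in the primary domain. The resulting estimate need not be the total intention-to-treat effect.

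That this is the wrong adjustment follows from the text alone. That it removes part of the effect is conditional on FITT changing incidents, which is intended but not known. Under the assumed paths of 0.36 SD and 0.3 to 0.5, without a common cause, the loss is about 15 to 25% of the planned 0.72 SD; it is 0% if incidents do not change. The planned power of 0.81 leaves little room, since a 10% loss already takes it to about 0.72. The plan should be corrected before analysis because the primary estimate is affected.

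**What to change.** - Delete new IPV incidents from the covariate set of the primary and secondary models, in all three places where section {20a} lists it, and keep it as an outcome with its own model.
- State that the remaining covariates (child functioning, parental psychopathology, duration and severity of violence) are T0 values.
- If an incident-adjusted model is wanted, for example to study mechanism, report it only as a labelled mediation or sensitivity analysis.
- Optionally add site as a fixed effect, since families are randomised within site.

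The cost is a change of wording. T0 values are already scheduled in Table 3 and site is known for every family. No new data are needed, and site would use a few degrees of freedom.

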### Outcomes {12}

Table 3 presents an overview of the time points for each outcome measurement.

**Table 3 Tab3:** Measures

	*Measures*				Measurement			
	Measure	Items	Respondent*	Type	T(0)	T(1–11)	T(12/14)	T(13)
Child PTSD	CAPS-CA		c	Interview	*			*
	CRIES	13	cp	Questionnaire	*	*	*	*
	TSCC	54	c	Questionnaire	*		*	*
Child functioning	SDQ	25	cp	Questionnaire	*		*	*
	CDI	28	c	Questionnaire	*		*	*
	CDC	20	p	Questionnaire	*		*	*
Parent functioning	NOSI-K	25	p	Questionnaire	*	*	*	*
	Trauma-informed	6	p	Questionnaire	*		*	*
	IES-r	22	p	Questionnaire	*		*	*
	YAS-R	29	p	Questionnaire	*		*	*
	DPAS	9	p	Questionnaire	*		*	*
Structural emotional and physical safety	CTS	77	p	Questionnaire	*		*	*
	CTS-pc	27+39	c	Questionnaire	*		*	*
	PRTI	21	p	Questionnaire	*		*	*
	ACE-Q	10	p	Questionnaire	*		*	*
	New IPV incidents	8	cp	Questionnaire	*	*	*	*
	SIS	43	c	Questionnaire	*		*	*
	SIFS	7	c	Questionnaire	*		*	*
	SIM-PR	28	p	Questionnaire	*		*	*
	Security scales	15	cp	Questionnaire	*		*	*
	FIT	4 tasks	cp	Observation			*	
Total items child					232	21	232	232
Total items parent					335	46	335	335

Marked measures are part of routine outcome measuring

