#### Sample size {14}

Power analysis was conducted to determine whether an informative trial could be conducted given limitations imposed upon the maximum sample due to the duration of the study and size of the population of children indicated for trauma treatment, using G*power 3 [95]. Sample size calculation was made based on the assumptions of the primary objective and the first secondary objective. A priori, we decided that adding systemic intervention elements to individual trauma therapy would be justified if it would mean that on average at least one out of five children would have clinically significant benefit when given the full FITT compared to treatment without systemic elements (number needed to treat = 5; equivalent to *f* = 0.18).

For primary objective 1 (Does intensive trauma therapy with a family-based component (FITT) lead to a stronger reduction of trauma symptoms and stronger increase of structural emotional safety than intensive trauma therapy without this family-based component (ITT)?), the sample size was calculated based on between 2 groups by within effect with at least two measurements (pre, end/follow-up), setting *f* = 0.18 with a power of 80% and a significance level of 5% (two-sided). Default settings were used for the correlation among repeated measures (= 0.5) and non-sphericity correction (*ε* = 1). According to the power analysis, a total sample size of 64 children is required.

Secondary objective 1 (Does intensive trauma therapy with a family-based component (FITT) lead to faster reduction of trauma symptoms and increase of structural emotional safety than low-frequency trauma treatment with parent therapy and family sessions?) is based on two measurements (pre and intermediate/follow-up). In accordance with the first sample size calculation, we tested with setting *f* = 0.18 with a power of 80%, a significance level of 5% (two-sided) was used. Again, default settings were used for correlation among repeated measures (= 0.5) and non-sphericity correction (*ε* = 1). Based on this calculation, a total sample size of 64 children is required.

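### The confounders are named as covariates in models that test difference in change, without fixing their timing or form; T0 main effects leave that estimate unchanged, and time-varying entry adjusts for outcomes

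*Protocol article*

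**What the plan says.** All references are to the protocol article.

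- **Tested quantity.** Statistical methods {20a}: "First, to determine whether changes on continuous measures are different per treatment, we use linear mixed models". Sample size {14} is built on the same quantity: "the sample size was calculated based on between 2 groups by within effect with at least two measurements", one of them the pre-treatment measurement.
- **T0 is a modelled response.** Table 4 gives three time points for most mixed-model outcomes. Table 3 has only T0, T12/14 and T13 for those scales, so the three must include T0.
- **Covariates.** Statistical methods {20a}: "We control for the duration and severity of family violence [96], child functioning, parental psychopathology [97], and new incidents of family violence". A later paragraph adds intensity of interparental violence and says how they enter: "The variables are treated as covariables in the analyses mentioned below". No covariate-by-time term is named, nor whether T0 or repeated values are used.
- **The covariate scales are also outcomes.** The SDQ, CDI and CDC (child functioning) and the YAS-R (parental psychopathology) are measured at T0, T12/14 and T13 in Table 3 and have their own mixed models in Table 4. New incidents are also measured during treatment.

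**The concern.** A covariate that is constant within a child and enters as a main effect raises or lowers all of that child's measurements equally. The test concerns how the measurements change, so such a covariate cannot adjust it. The plan would then report control for prespecified confounders that has practically no effect on the tested contrast. With 32 children per arm, a chance imbalance in severity of violence or parental psychopathology would stay in the estimate, and any precision from covariates that predict change would not be gained.

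The other way to read the text is to use each visit's value. The covariate then does act on the test, but it is a post-randomisation variable that the parent and family component may itself improve, so part of the treatment effect is adjusted away. In the models for the SDQ, CDI, CDC and YAS-R the covariate would be the outcome itself.

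**Working it through.** **1. The plan's own figure.** With f = 0.18, two groups, m = 2 measurements and correlation 0.5, λ = f²·N·m/(1 − ρ) = 0.0324 × 64 × 2/0.5 = 8.29 on 1 and 62 df. Power is 0.809 at N = 64 and 0.796 at N = 62, so 64 reproduces. So do 96 over three arms and 96/0.8 = 120. As a standardised difference in change, √(4 × 8.29/64) = 0.72 SD.

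**2. Algebra.** For child i at time t, y_it = τ_t + γg_i + δ_t·g_i + βx_i + b_i + e_it. Subtracting T0 gives τ_t − τ_0 + (δ_t − δ_0)g_i + e_it − e_i0. The term βx_i is gone. With a covariate-by-time term β_t·x_i, the part (β_t − β_0)x_i remains and adjusts the contrast.

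**3. Simulation, complete data.** Assumed: 32 per arm, three times, true difference in change −0.40, covariate slope on change 0.4, covariate imbalance 0.3 SD, random-intercept model fitted by ML, 200 runs. In the time-varying row, treatment also lowers the covariate by 0.3 after T0.

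| Covariate entry | Mean estimate, last time point | Mean SE |
|---|---|---|
| none | −0.317 | 0.257 |
| T0 main effect | −0.317 | 0.257 |
| T0 by time | −0.444 | 0.246 |
| time-varying | −0.222 | 0.271 |

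The sizes depend on the assumptions; the equality of the first two rows does not. Their largest difference was 9e-15 in the estimate and 5e-6 in the SE. A single fit with an unstructured covariance and four covariates gave −0.58058 (SE 0.32596) both without covariates and with main effects, and −0.487 with covariate-by-time terms.

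**4. Covariance structure.** The SE is unchanged under unstructured and compound-symmetric covariance. It is not unchanged under every structure: in example fits it moved from 0.330 to 0.310 under AR(1) and from 0.452 to 0.358 under a diagonal structure. Those structures tie the variance of change to the variance of level. The estimate itself does not move, so its true sampling variance does not either.

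**5. Dropout.** The plan says: "To handle missing data, we will use maximum likelihood estimation within the linear mixed model analyses". In one data set with about 20% missing at T13, the estimate was −0.541 without the covariate, −0.524 with the main effect and −0.609 with covariate-by-time. With about 20% missing at all post-baseline visits the three were −0.509, −0.491 and −0.568. The main effect moves the estimate by about 0.02, here away from the adjusted value.

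**6. Chance imbalance.** The SD of a standardised covariate's mean difference is √(2/32) = 0.25, so P(|difference| > 0.4) = P(|Z| > 1.6) = 0.11. At 0.4 SD, a covariate explaining share R² of change shifts the estimate by 0.4·√R². That is 0.13, 0.18 or 0.22 SD at R² of 10%, 20% or 30%, or 18%, 25% or 30% of 0.72.

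**7. Power if entered properly.** Divide λ by (1 − R²)(1 + p/(64 − p − 3)), with 62 − p df. R² is not in the documents, so a range is shown.

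| R² | p = 4 | p = 6 | p = 8 |
|---|---|---|---|
| 10% | 0.823 | 0.809 | 0.794 |
| 20% | 0.864 | 0.852 | 0.838 |
| 30% | 0.905 | 0.895 | 0.883 |

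Unadjusted power is 0.809. Statistical methods {20a} names six covariates; using all three child-functioning scales makes eight.

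**The case against.** The strongest reply is that the article never writes the model out. It does not exclude covariate-by-time terms or restrict covariates to T0, and such detail often sits in an analysis plan that is not shown. The section also says "We will use the end of treatment (T12/T14) and intermediate/follow-up time-point (T13) to compare FITT with ITT (objective 1", which could describe a model with post-treatment responses only. There, adjustment works: with the T0 outcome on the right-hand side, adding the covariate moved an example estimate from −0.349 (SE 0.229) to −0.410 (SE 0.189).

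This stands in part. A reader might infer that the promised control is certain not to happen. The documents do not support that, because the model form is open. But the article does state the test, the covariates and their role, and both plain readings of that change model serve it badly. That is more than omitted detail.

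Three further inferences would also go too far.

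- **Confounding.** Arms are randomised, so an unadjusted comparison is not systematically confounded.
- **All primary outcomes.** CAPS-CA is analysed by GEE. In an example logit GEE, a main effect moved the interaction from −0.344 to −0.416, so the cancellation does not carry over.
- **All listed covariates.** New incidents vary over time and do not cancel; their difficulty is that they arise after randomisation.

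**Conclusion.** The point holds conditionally, for the linear mixed models of change. With T0 main effects and complete data, the named covariates leave the group-by-time estimate exactly unchanged; with dropout of the planned size, nearly unchanged. The cost is uncorrected chance imbalance and forgone precision. With time-varying entry the estimate changes, but by adjusting for outcomes of the trial.

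The imbalance figures and any power gain rest on an assumed R². With four covariates, power rises from 0.81 to between 0.82 and 0.90 for R² of 10% to 30%. With six covariates at R² = 10% there is no gain, and with eight a small loss. This is worth settling before analysis because the correction is nearly free, but it does not undermine the trial's validity.

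**What to change.** In Statistical methods {20a}, state that violence history, child functioning and parental psychopathology enter as T0 values, and choose one of two models:

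1. the change model with T0 as a response, adding a covariate-by-time term for each covariate; or
2. a model whose responses are T12/T14 and T13, with the T0 outcome and the T0 covariates on the right-hand side.

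These are distinct models and need not give the same estimate, so one should be named as primary. Keep the covariate set small, for example one prespecified scale per construct. Leave a covariate out of the model for its own scale, apart from the T0 outcome term in the second model. Keep new incidents during follow-up out of the primary model and use them only in a sensitivity analysis.

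The change is to wording only and needs no new data. It costs a few degrees of freedom, which is why the number of covariates matters at 64 children.
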